#### Primary outcomes

The primary outcome is the reduction of modifiable unhealthy lifestyles immediately after intervention (6 months). Unhealthy lifestyles considered comprise smoking, excess alcohol consumption, physical inactivity, unbalanced diet, and overweight/obesity (representing balance between energy intake and energy expenditure). Items as formulated in the Healthy Lifestyle Index Score (HLIS) from the European Prospective Investigation into Cancer and Nutrition cohort study [41], will be used to measure these lifestyles (see Table 2). Assessment of body mass index (BMI) and categorization into overweight/obesity will rely on relevant recommendations according to Chinese guidelines [42], while dietary index is based on the Mediterranean Diet Score [43]. For reasons of simplicity each lifestyle will be coded as a dichotomous variable with 0 indicating absence, 1 indicating presence of a particular unhealthy lifestyle. The decrease of unhealthy lifestyles by at least one at 6 months is considered favorable.

**Table 2 Tab2:** Components of lifestyle risk score

Components	Score	Measurement	Definitions in the study
Smoking status	0–4	Questionnaire • History of smoking in the past	Never = 4, ex-smokers quit > 10 years = 3, ex-smokers quit ≤ 10 years = 2, current ≤ 15 cigarettes/day = 1, current > 15 cigarettes/day = 0 [41]
Alcohol intake	0–4	Questionnaire • Alcoholic beverage consumption per day	low consumption of alcohol (< 6.0 g/day = 4, 6.0–11.9 g/day = 3, 12.0–23.9 g/day = 2, 24.0–59.9 g/day = 1, 60 + g/day = 0) [41, 44]
Physical activity	0–4	International Physical Activity Questionnaire • Number of hours per week spent in moderate to vigorous activities, vigorous-intensity PA	Metabolic equivalent tasks for four activity domains (occupational PA; transportation PA; PA for housework; sports and leisure-time PA): fifth quintile = 4, fourth quintile = 3, third quintile = 2, second quintile = 1, first quintile = 0 [41]
Dietary factors	0–4	Food Frequency Questionnaire • MDS, a linear score that incorporates 9 nutritional components of the Mediterranean diet [45]	Scoring 4 to 0 points for top to bottom quintile of the MDS: fifth quintile = 4, fourth quintile = 3, third quintile = 2, second quintile = 1, first quintile = 0 [44]
Overweight/obesity	0–4	Medical examination • BMI	< 22 = 4, 22–23.9 = 3, 24–25.9 = 2, 26–27.9 = 1, ≥ 28 = 0 [46]
Total score	0–20	Total of unweighted five components	

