#### Secondary outcomes

Secondary outcomes include modifications of unhealthy lifestyles at 3, 9, and 12 months, and modifications of specific lifestyles (also including smoking, alcohol consumption, physical activity, diet, and BMI), sleep quality, drug intake adherence, smoking/drinking quitting, mental health outcomes, cognitive function, self-efficacy, implicit health attitudes, social support, frailty, and clinical outcomes at baseline, 3, 6, 9 and 12 months, with details as follows:

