##### Frailty

Frailty will be assessed with the Phenotype of Frailty scale [57].

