### Data analysis

Data analyses will be performed using R version 4.2.1 for Windows. All data will be securely stored in an electronic database and accessible only to researchers who meet the criteria as provided in the research ethics approval document.

Descriptive statistics will be provided for the baseline sample. Categorical variables will be summarized in terms of frequencies and percentage, in total and by intervention group. Continues variables will be summarized as mean ± standard or median (interquartile range) in total and by intervention group.

All main analyses will be performed on intention to treat (ITT) basis. The primary outcome will be analyzed with mixed effects log-linear Poisson regression of any reduction of unhealthy lifestyles at six months (favorable outcome vs not) on intervention group as randomized at baseline [58]. In addition, the model will include a random intercept for subject nested in village and a fixed effect for town (as number of clusters not sufficient for variance estimation in the latter case). Treatment effect at six months (immediately after intervention) will be provided as relative risk ratio [59]. As regards secondary outcomes, reduction of unhealthy lifestyles (favorable outcome vs. not) at all timepoints will be simultaneously analyzed with longitudinal mixed effects log-linear Poisson regression on timepoint, and an interaction term of timepoint and intervention group, with random intercepts for subject nested in village and fixed effect for town as specified for the primary outcome. Other binary outcomes including smoking/drinking quitting, drug intake adherence, frailty will be analyzed in the same fashion. For continuous outcomes including sleep quality, smoking/drinking carving, mental health outcomes, cognitive function, self-efficacy, implicit health attitude, social support, longitudinal analysis of covariance (ANCOVA) models with time and time-group interaction will be estimated, adjusted for the respective outcome at baseline and featuring random intercepts for subject nested in village as well as a fixed effect for town [60]. Estimates of differences in changes in lifestyles between groups at 3, 6, 9, and 12 months will be analyzed post hoc using Wald-tests.

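### Drug intake adherence and frailty are sent to a model written for a change outcome, which has no baseline term, so precision is lost if they are analysed as states

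*Protocol article*

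**What the plan says.** All references are to the protocol article.

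- **The model and its outcome.** Data analysis says that "reduction of unhealthy lifestyles (favorable outcome vs. not) at all timepoints will be simultaneously analyzed", using "longitudinal mixed effects log-linear Poisson regression on timepoint, and an interaction term of timepoint and intervention group". It adds random intercepts for subject nested in village and a fixed effect for town. No baseline-outcome term is listed.
- **What that outcome is.** Primary outcomes defines success as a change: "The decrease of unhealthy lifestyles by at least one at 6 months is considered favorable".
- **Which outcomes inherit the model.** The next sentence of Data analysis reads "Other binary outcomes including smoking/drinking quitting, drug intake adherence, frailty will be analyzed in the same fashion".
- **How continuous outcomes are handled.** The sentence after that gives them a longitudinal ANCOVA with time and time-by-group terms, "adjusted for the respective outcome at baseline and featuring random intercepts for subject nested in village as well as a fixed effect for town".
- **What is measured.** Secondary outcomes schedules "social support, frailty, and clinical outcomes at baseline, 3, 6, 9 and 12 months", in a list that also contains drug intake adherence. The Frailty section says only "Frailty will be assessed with the Phenotype of Frailty scale". The section on drug intake adherence describes a scale about missed doses and medication behaviour. Neither defines a change.
- **Other adjustment.** The adjusted models under Sensitivity analysis add age and gender only. The balancing covariates named under Randomization are number of residents, mean age and sex ratio.

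**The concern.** A model without a baseline term suits an outcome that is already a change from baseline. Carried over to an outcome recorded as present or absent at each visit, the same terms leave the starting state out. A participant who was frail at entry then counts as an event at follow-up with no allowance for where they started.

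The protocol adjusts its continuous outcomes for baseline and gives no reason for treating these two differently. Two things are at stake. One is precision from data collected before randomization in any case. The other is sensitivity of the estimate to a chance difference between arms at entry, when only 20 villages are randomized and neither state is among the named balancing covariates.

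**Working it through.** **1. Side by side**

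| | Lifestyle reduction | Drug adherence, frailty | Continuous outcomes |
|---|---|---|---|
| Outcome as described | change from baseline | instrument reading at a visit | score at a visit |
| Measured at baseline | yes | yes | yes |
| Baseline in the analysis | inside the outcome | not stated | covariate |

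The middle column is the gap. Smoking/drinking quitting, named in the same sentence, belongs with the first column because quitting is a change.

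**2. Would baseline rows repair it?** Suppose baseline is entered as an extra timepoint. In a linear check with two visits, 100 people per arm and within-person correlation 0.6:
- with a free group difference at every visit, the follow-up contrast equals the raw follow-up difference, −0.170;
- with the arms constrained equal at baseline, it becomes −0.157, which is the raw difference minus 0.6 times the baseline difference.

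So a subject intercept plus baseline rows adjusts the contrast only under that constraint, and the protocol does not state it.

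**3. How large is chance imbalance?** No prevalence or intracluster correlation (ICC) is given for either outcome. Assume prevalence 20% and ICC 0.03. With the recruitment target of 128 per arm in 10 villages (12.8 per village):

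SD of the baseline arm difference = √[2 × 0.2 × 0.8 / 128 × (1 + 11.8 × 0.03)] = √(0.0025 × 1.354) = 0.058, about 6 percentage points.

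At a baseline to follow-up correlation of 0.5, about half of any such difference carries into follow-up. With 102 per arm and no clustering, the SD is √(2 × 0.1 × 0.9 / 102) = 0.042 at 10% prevalence and √(2 × 0.4 × 0.6 / 102) = 0.069 at 40%.

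**4. What does adjustment gain?** As a linear guide, adjustment multiplies the variance by 1 − ρ², and power becomes Φ(d/√(1 − ρ²) − 1.96), where d = 1.96 + z(power).
- ρ = 0.3: 0.50 becomes 0.538, and 0.80 becomes 0.836.
- ρ = 0.5: 0.50 becomes 0.619, and 0.80 becomes 0.899.

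Two simulations, each with 20 villages of 10 participants and 20% prevalence, give a closer picture:

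| Simulation | Correlation | Unadjusted power | Adjusted power | Gain (points) |
|---|---|---|---|---|
| A: village-mean t-test, ICC 0.03, true RR 0.5 | 0.3 | 0.46 | 0.49 | 3 |
| A | 0.5 | 0.45 | 0.54 | 9 |
| A | 0.7 | 0.43 | 0.64 | 21 |
| B: log-link Poisson, cluster-robust errors, true RR 0.6 | 0.5 | 0.333 | 0.407 | 7 |
| B | 0.7 | 0.326 | 0.494 | 17 |

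In A, subtracting baseline instead of adjusting for it gave power 0.28, 0.36 and 0.48 at correlations 0.3, 0.5 and 0.7. That is below adjustment throughout.

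**5. Is the unadjusted analysis biased?** No. Setup B was run under no effect, with prevalence 10% to 40% and correlation 0.3 to 0.7. The mean log RR was about 0 and rejection was 0.05 to 0.08, with or without the baseline term. What differed was how far the estimate followed the chance baseline difference: correlation 0.32 to 0.76 unadjusted, 0.01 to 0.20 adjusted. The SD of the log RR fell from 0.468 to 0.443 (10%, 0.3), from 0.324 to 0.263 (20%, 0.5) and from 0.193 to 0.126 (40%, 0.7).

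**The case against.** **The analysis is already valid.** Comparing randomized arms at follow-up is unbiased, and chance imbalance is part of the sampling error that the standard error reflects. This stands. A reader might infer that baseline differences would be reported as a false intervention effect. Neither the documents nor step 5 supports that.

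**The coding is not stated.** The protocol names the instruments but not the binary variable. The secondary outcome list opens by speaking of modifications, and the template outcome is itself a change, so adherence and frailty might be coded as improved or not. This stands in part, and it is why the point is conditional on their being analysed as states.

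**The model may already constrain baseline.** The listed terms are timepoint and timepoint by group, with no group main effect. If baseline is the reference timepoint, the arms could be equal there by construction, and step 2 shows that this would adjust the contrast. The reading is possible but unstated. It fits poorly with a template outcome that has no value at baseline, and the lifestyle contrasts are listed only at 3, 6, 9 and 12 months.

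**The size is assumed.** This stands. Prevalence, ICC, correlation and true effect are not in the documents, and both simulations simplify the planned random-intercept model. Adherence can be assessed only in people taking medication, a number the protocol does not give.

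**Detail belongs in an analysis plan.** This carries less weight, because the article itself states the model terms and assigns these outcomes to them.

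**Conclusion.** The point holds as an efficiency matter for two secondary outcomes. On the plain reading, drug intake adherence and frailty go to a model with no baseline-outcome term, while the continuous outcomes are "adjusted for the respective outcome at baseline". If they are analysed as states, the cost is lost precision and greater exposure to chance imbalance with 10 villages per arm.

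Under the assumptions shown, adjustment is worth about 3 to 4 power points at correlation 0.3 (simulation and linear guide together). In the simulations it is worth 7 to 9 points at 0.5 and 17 to 21 at 0.7. These are rough guides; simulation error alone could move them by a point or two.

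It would go too far to call the planned comparison invalid, or to extend the point to the primary model or the sample size. The primary outcome contains its own baseline, and the stated sample size concerns that outcome alone. This is a free or cheap improvement that the trial team could reasonably make.

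**What to change.** In Data analysis, give these two outcomes their own sentence, for example: *Drug intake adherence and frailty will be analysed with the same longitudinal model on the 3-, 6-, 9- and 12-month visits, adjusted for the respective status at baseline.* An alternative with the same purpose is to include baseline as a timepoint and state that the arms are constrained to be equal there. Leave smoking/drinking quitting as it is. If either outcome is in fact meant to be coded as improved or not, say so instead.

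The cost is one clause and one model term. The data are already due to be collected before randomization, so no visit or sample size changes. The downside is an extra parameter in a binary model where events may be few. The choice should be recorded before group labels are revealed, so that it does not depend on how the arms turn out at baseline.

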#### Tools for intervention implementation

Intervention and control groups in each community will be assigned one trained group manager and one local medical doctor or nurse with at least 5 years professional experience. The 3SLIFE intervention will be implemented through online and offline activities. Online interventions will be delivered through WeChat and Tiktok Channels, two mainstream live streaming apps in China, to guide diet, exercise, and medication, etc. For online activities, group manager and local physicians will provide healthy lifestyle information and skills (e.g., exercise guidance, recipes) as well as self-management skills with the support of health tools (e.g., fitness aids such as elastic bands) in WeChat groups and one-on-one communication by WeChat or phone. Offline interventions will be guided by cognitive behavior therapy (CBT) [40] at local health centers through group managers, with group managers and physicians designing and recording related healthy lifestyle promotion activities. During the intervention, investigators will record participants' responses and satisfaction with the intervention and obtain their daily health records (e.g., photos of meal preparation following recommended recipes). For individuals with good adherence to the intervention or improved physical examination indicators, value-added gifts (e.g., household goods) will be released as rewards.

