The 3SLIFE trial aims to provide a multi-level theoretical framework for mhealth interventions to develop and maintain multi-dimensional healthy lifestyles in Chinese community residents. Several strength warrant mentioning: First, since lifestyles are often clustered, and in additive or synergistic manner increase the risk of multiple chronic diseases, a multi-dimensional healthy lifestyle intervention, which considers the five main unhealthy lifestyles as suggested by previous large-sample size studies, may be more conducive to overall and sustained health outcomes [37, 68, 69]. Second, the strategies of 3SLIFE will be guided by socioecological model and supported by multi-dimensional empowerment approach, which may overcome the shortcomings of both approaches when taken alone, that is lack of an agency dimension in the socioecological model and lack of a clear multi-level environmental dimension in the empowerment approach. Third, several approaches based on multi-dimensional empowerment will be used to promote self-management-oriented lifestyle changes, such as participants’ voluntarily documentation of their daily lifestyle in WeChat groups, and documentation encouraged by family members or medical staff, which will determine the mHealth adoption and utilization as well as lifestyle changes and sustainability. Fourth, the strategies of 3SLIFE will combine online and offline approaches for lifestyle intervention, which may help participants to become more familiar with smart devices and social media apps and increase trust between participants and medical staff. Fifth, this study will conduct a 6-month follow-up, to evaluate sustainability of intervention effects.

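### For the continuous secondary outcomes, the longitudinal ANCOVA models have no village-by-visit variance, so between-visit arm contrasts are over-precise if village effects vary over time

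*Protocol article*

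**What the plan says.** All of the model wording is in the Data analysis section of the protocol article.

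- **Continuous secondary outcomes** (sleep quality, craving, mental health, cognition, self-efficacy, health attitudes, social support): longitudinal ANCOVA on time and its interaction with arm, with the baseline value as covariate. The random part reads "featuring random intercepts for subject nested in village as well as a fixed effect for town".
- **Binary longitudinal outcomes**: "longitudinal mixed effects log-linear Poisson regression on timepoint, and an interaction term of timepoint and intervention group". The random part is again one village and one subject intercept, and town is fixed.
- **Tests**: "Estimates of differences in changes in lifestyles between groups at 3, 6, 9, and 12 months will be analyzed post hoc using Wald-tests".

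The section names no village-by-visit effect, random slope or cluster-robust variance, and the Sensitivity analysis section adds none. The primary analysis is a separate model at 6 months only.

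Two other places bear on the point. The Discussion lists as a strength that "this study will conduct a 6-month follow-up, to evaluate sustainability of intervention effects". Under Tools for intervention implementation, "Intervention and control groups in each community will be assigned one trained group manager", together with a local doctor or nurse.

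**The concern.** Villages are randomized, ten per arm. How far an arm changes between two visits must therefore be judged against how far whole villages change between those visits. In a model with constant village and subject intercepts, both intercepts cancel from a between-visit contrast. Its standard error then rests on the residual alone, and any shift shared by a village is treated as independent noise across its members.

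Such shifts are plausible here. Each community has its own manager and clinician, activities are held monthly for the whole group, and instructed delivery stops at month 6. Whether an effect is maintained or decays after month 6 is a between-visit question. For the continuous outcomes it would be read from the time-by-group terms, which is where the error term is weakest.

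**Working it through.** **Plan's own figure.** The protocol gives no figure for the longitudinal models. Its sample size, used here only for village size, reproduces. For 2% vs 12%, two-sided 5% and 80% power with pooled variance: [1.96·√(2·0.07·0.93) + 0.8416·√(0.0196 + 0.1056)]² / 0.10² = 101.0, rounded up to 102 per arm (204). Then 102/0.8 = 127.5, rounded up to 128 per arm (256). Over 20 villages this is m = 256/20 = 12.8 persons recruited and 204/20 = 10.2 retained.

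**Assumptions, because the protocol gives none.** Total variance 1. Village ICC 0.02, 0.05 or 0.10. Correlation of village effects between visits (CAC) 0.8 or 0.5. Within-person correlation 0.6, so the part that varies by visit (village-by-visit plus residual) is 0.4.

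**Formula.** For a between-visit arm contrast, true variance / model variance is close to VR = 1 + (m − 1)·rho, with rho = ICC·(1 − CAC)/0.4. The SE is too small by 1 − 1/√VR. True type I error is 2·[1 − Φ(1.96/√VR)] for one contrast, and P(χ²₃ > 7.815/VR) for the joint time-by-group test over four visits.

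Example (ICC 0.05, CAC 0.8, m = 12.8): rho = 0.01/0.4 = 0.025; VR = 1 + 11.8·0.025 = 1.295; √VR = 1.138; SE low by 12%.

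| ICC, CAC | rho | VR (m = 12.8) | SE low by | 12 vs 6 months | Joint test | Joint test, m = 10.2 |
|---|---|---|---|---|---|---|
| 0.02, 0.8 | 0.010 | 1.118 | 5% | 0.064 | 0.07 | 0.07 |
| 0.05, 0.8 | 0.025 | 1.295 | 12% | 0.085 | 0.11 | 0.10 |
| 0.10, 0.8 | 0.050 | 1.590 | 21% | 0.120 | 0.18 | 0.15 |
| 0.05, 0.5 | 0.0625 | 1.738 | 24% | 0.137 | 0.21 | 0.18 |
| 0.10, 0.5 | 0.125 | 2.475 | 36% | 0.213 | 0.37 | 0.30 |

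**Simulation of the planned model.** Balanced Gaussian data, no arm effect, 20 villages of 13, four visits, 4,000 runs per setting; town and the baseline covariate omitted. The joint test rejected in 0.067, 0.117, 0.195, 0.215 and 0.377 of runs, in the order of the table, and in 0.057 with CAC = 1. The planned model pools village-by-visit (18·3 = 54 df) with subject-by-visit (20·12·3 = 720 df) into one residual on 774 df. Tested against the village-by-visit mean square on 54 df, the joint test rejected in 0.046–0.058.

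**Single-visit arm differences.** Here the village intercept stays in the standard error and absorbs part of the omitted variance. A separate simulation with 10 or 13 per village and within-person correlation near 0.5 gave true/model SE ratios at 12 months, ICC 0.05, of about 1.01–1.05 (CAC 0.8) and 1.06–1.07 (CAC 0.5). Type I error was 0.058–0.065 and 0.075. With CAC = 1 it was already 0.058–0.059, because a normal reference is used with only 20 villages. Over all settings the range is about 5.5–10%.

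**Binary outcomes (Poisson).** A Poisson model has no free residual variance: it fixes the within-person variance at p. The true within-person variance of a binary outcome is about p(1 − p)(1 − r). At 12% favorable (the protocol's intervention-arm rate, assumed here for both arms and all visits) and r = 0.6 that is 0.12·0.88·0.4 = 0.042, against a model value of 0.12, a ratio of 2.84. This exceeds every VR in the table. A null binary simulation (20 villages of 13, four visits, 2,000 runs per setting) gave joint type I error of 0.000, 0.001, 0.005, 0.002 and 0.033, and true/model SE ratios for 12 vs 6 months of 0.64, 0.70, 0.80, 0.79 and 0.97. With r lowered to 0.4, the worst case reached 0.056 for the joint test and 0.068 for the single contrast.

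**The case against.** Four points can be made for the plan.

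- **The listed tests.** With time and time-by-group terms, no separate group effect and baseline as covariate, the Wald tests read most naturally as arm differences at each visit. Neither a 12-versus-6-month contrast nor a joint interaction test is named. This stands and limits the reach. It does not remove the point, because the interaction is in the model and a statement on maintenance needs a comparison between visits.
- **The size is assumed.** This stands. The larger figures need ICC 0.10 or CAC 0.5, and they shrink at 10 persons per village.
- **The binary outcomes.** A reader might infer that every longitudinal analysis is affected, including the reduction in unhealthy lifestyles that mainly carries the sustainability question. The documents do not support that. Those outcomes are analysed by Poisson regression, where the planned tests are mostly conservative and an added village-by-visit variance would tend to be estimated at zero.
- **Detail for an analysis plan.** The structure of random effects in secondary models is often settled in the SAP, which is not shown. Here, however, the article does state the random part, and it can be assessed as stated.

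**Conclusion.** The point holds for the continuous secondary outcomes only, and only if village effects vary between visits. Under the stated assumptions the joint interaction test then runs at about 7–38% instead of 5%, a 12-versus-6-month contrast at about 6–21%, and visit-specific differences at about 5.5–10%. A reader might take it as established that these intervals are too narrow. The protocol does not support that, since it gives neither an ICC nor a correlation over time, and constant village effects would produce no material excess from this source. The 6-month primary analysis is untouched. A small-sample degrees-of-freedom correction alone would not cure the between-visit contrasts, because what is missing is a variance component. This is a cheap and worthwhile correction to secondary analyses and does not threaten the trial's main result.

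**What to change.** In the continuous-outcome ANCOVA models, add a random intercept for village-by-visit to those for village and for subject within village. Take both the visit-specific and the between-visit group contrasts from that model, and name the contrast that answers the sustainability question for these outcomes. If the model does not fit, analyse village means per visit instead. The Poisson models and the primary analysis need no change on this account.

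The cost is one variance term and somewhat wider intervals for between-visit contrasts. With 20 villages the added variance may be estimated as zero, in which case the fit returns to the planned model.

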### Settings and participants

The study will be embedded in the China Multi-Ethnic Cohort (CMEC) [33], which uses a multistage random sampling strategy to select participants. Four towns (administrative areas in China with about 300,000 inhabitants) will be randomly selected from 18 towns that have undergone two survey waves within the CMEC, and used as the study sites. A total of 20 eligible communities/villages will further be randomly selected within the four towns. These will then be randomized to control or intervention. Eventually, community-dwelling adults from these communities/villages will be screened for eligibility and those who meet the eligible criteria will be invited to participate.

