### Randomization and allocation concealment

In this cluster-RCT, recruitment and baseline data collection will be conducted prior to randomization. Cluster randomization, which is necessary for implementation of community-level interventions, mitigates concerns of within-community/village contamination, and improves the feasibility of on-site intervention, will be performed at the community/village level. A total of 20 eligible communities/villages will be randomized using a computer-based random number generator (www.random.org) and assigned to either the intervention group or the control group, with 10 communities/villages in each group. A covariate adaptive procedure will be used to minimize the *P* value from a joint *F* test (1000 iterations) to facilitate covariate balance [34, 35]. Several location level covariates will be considered, including number of village residents, and mean age and sex ratio of residents.

Allocation concealment will be ensured through central randomization [36]. Specifically, an independent statistician will generate a block randomization sequence with randomly permutated block size (4–8) and 1:1 allocation ratio. A sequential list with resulting random numbers will be provided to the study center that recruits villages. Only after participation of a village is confirmed, will the study center reveal labels of the random sequence to the trial team delivering interventions.

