#### Subgroup analysis

We will conduct exploratory subgroup analyses by sex, age, and drug intake adherence. To explore heterogeneity of intervention effects by subgroup, we will include an interaction term between intervention assignment and subgroup in models, and statistical significance will be determined with Wald tests.

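### Treatment is assigned to 20 villages, yet the Wald tests named for group differences carry no small-cluster correction; against a normal reference, intervals for continuous outcomes could be up to about 8% too narrow

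*Protocol article*

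**What the plan says.** Under Randomization and allocation concealment, allocation "will be performed at the community/village level", "with 10 communities/villages in each group". Settings and participants gives four towns.

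Under Data analysis, the primary model has "a random intercept for subject nested in village and a fixed effect for town (as number of clusters not sufficient for variance estimation" at town level). For the continuous scales, "longitudinal analysis of covariance (ANCOVA) models with time and time-group interaction will be estimated", adjusted for baseline and with the same random intercepts and town effect. On testing, the section says: "Estimates of differences in changes in lifestyles between groups at 3, 6, 9, and 12 months will be analyzed post hoc using Wald-tests". Subgroup analysis adds that, for interactions, "statistical significance will be determined with Wald tests".

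The article does not say whether the Wald statistics are referred to a normal, t or F distribution, whether the linear models are fitted by REML or ML, or what village ICC is expected.

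**The concern.** Participants in a village share an allocation, so the treatment effect is a comparison between villages. Its precision rests on a village variance estimated from 20 units, however many participants each village supplies. A Wald test against the normal distribution treats that variance as known. With about 15 degrees of freedom it is not, and the test rejects too often unless the village variance is very small.

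The authors recognise this kind of problem one level up: town is a fixed effect because four towns are too few to estimate a variance. The reasoning is not carried to the village level, where treatment is assigned. At stake are the continuous secondary outcomes (such as sleep quality, mental health, cognition, self-efficacy and social support), each analysed over several time points.

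**Working it through.** **Inputs from the protocol.** 20 villages, 10 per arm; 4 towns; 256 recruited and 204 needed for analysis. That is 256/20 = 12.8 recruited and 204/20 = 10.2 analysed per village, so 10 and 13 were used. The protocol states no degrees of freedom or interval width, so there is no figure of its own to reproduce.

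**Assumptions.** Village ICC from 0 to 0.20 (for ANCOVA, the ICC left after baseline adjustment); five villages per town; equal village sizes; one time point; two-sided 5% level.

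**Degrees of freedom.** Villages minus intercept, arm and three town terms: 20 - 1 - 1 - 3 = 15. Without town: 20 - 2 = 18.

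**Interval width.**
- 15 degrees of freedom: t = 2.131 against z = 1.960. The ratio is 1.087, so the corrected interval is 8.7% wider. Equivalently, the normal interval is 1 - 1.960/2.131 = 8.0% too narrow.
- 18 degrees of freedom: t = 2.101, giving 7.2% wider, or 6.7% too narrow.
- The true level of a 1.96 cut-off is P(|t| > 1.96) = 6.9% with 15 degrees of freedom and 6.6% with 18.

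**Dependence on the ICC.** A random-intercept linear model with fixed town effects and no treatment effect was simulated 100,000 times per setting. Type I error, 10 / 13 participants per village:

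| Assumed ICC | REML, normal | REML, t(15) | ML, normal |
|---|---|---|---|
| 0 | 4.3% / 4.2% | 2.8% / 2.7% | 5.3% / 5.1% |
| 0.01 | 4.8% / 4.9% | 3.2% / 3.3% | 6.1% / 6.3% |
| 0.05 | 6.0% / 6.3% | 4.2% / 4.4% | 8.7% / 9.2% |
| 0.10 | 6.6% / 6.8% | 4.8% / 4.9% | 10.3% / 10.6% |
| 0.20 | 6.9% / 6.9% | 5.0% / 5.0% | 11.0% / 11.0% |

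At ICC 0.02, 20,000 runs with REML and a normal reference gave 5.1-5.5%. Under REML the problem is close to nil at 0.02 or below and approaches its limit of 6.9% from about 0.10. ML is worse because it also underestimates the village variance.

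**Binary outcome.** A Poisson model overstates the variance of a binary outcome, which could offset the missing correction. At the protocol's planning rates of 2% and 12% the offset is small. Per participant per arm, the variance of the log relative risk is 1/0.02 + 1/0.12 = 58.33 under Poisson and 0.98/0.02 + 0.88/0.12 = 56.33 under the binomial. The standard error is overstated by √(58.33/56.33) - 1 = 1.8%, against a shortfall of up to 8.7%. With so few events other approximations also matter, so no error rate is claimed for the binary outcome.

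**The case against.** The strongest objection is that a large-sample test is nowhere stated. A reader might infer one from the word Wald, but a Wald statistic can be referred to a t or F distribution with Satterthwaite, Kenward-Roger or between-within degrees of freedom. An article may leave that choice to an analysis plan. This stands: no error is established. What survives is that the protocol goes beyond silence. It names a test, and it discusses too few clusters for town but not for village.

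The sentence on Wald tests also concerns changes in lifestyles, and no test is named separately for the continuous scales. Applying it to them is an inference, though the models share the same structure.

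A reader might take a fixed shortfall of about 9% from the ratio 1.087. That mistakes wider for narrower, and it ignores the dependence on reference distribution, fitting method and ICC.

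A reader might also extend the point to the subgroup tests. The documents do not support this. Sex, age and drug adherence vary within villages, so those interactions are estimated largely within villages, and they are labelled exploratory. In a simulated treatment-by-sex interaction (20 villages of 10, REML), the normal reference rejected 4.8%, 5.1% and 5.1% at ICCs of 0.05, 0.10 and 0.20. Using t(15) gave only 3.0-4.0%.

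Finally, the simulation in the table covers one time point in a balanced design. It reproduces neither the longitudinal fit nor the covariate-balancing allocation.

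**Conclusion.** The point holds as a conditional one. Treatment is assigned to 20 villages, and the only test named for group differences is a Wald test with no small-cluster correction. If that test uses a normal reference, intervals for continuous outcomes could be up to about 8% too narrow. Type I error would then be about 6-7% under REML and about 9-11% under ML at ICCs of 0.05-0.20. Under REML it would be near or below 5% at 0.02 or less.

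These sizes rest on an assumed ICC range, 15 degrees of freedom and a balanced single-time-point model. They include no allowance for multiple imputation. The exposure lies mainly in the continuous secondary outcomes; any effect on the primary conclusion is less clear.

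**What to change.** In Data analysis, state that:

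- linear mixed models are fitted by REML, with Satterthwaite or Kenward-Roger degrees of freedom for the treatment contrasts;
- treatment contrasts for binary outcomes use a named small-sample method, such as a t reference with between-within degrees of freedom, or a permutation test that redraws allocations by the procedure actually used under Randomization and allocation concealment.

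Leave the participant-level interaction tests in Subgroup analysis without village-based degrees of freedom.

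The cost is a sentence or two and a software option, best settled before unblinding. The statistical price is some conservatism when the village variance is near zero: type I error of about 3% at ICC 0 with t(15), hence some loss of power there. At ICCs of 0.05-0.20 the same reference gives 4.2-5.0%.
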